#### Assessments of fertility

Medical documentation of oophorectomy, hysterectomy, or tubal ligation must be retained as source documents. Subsequent hormone level assessment to confirm the woman is not of childbearing potential must also be available as source documentation in the following cases:

- Surgical bilateral oophorectomy without a hysterectomy
- Reported 12 months of natural (spontaneous) amenorrhea with an appropriate clinical profile.

In the absence of the above medical documentation, LH and FSH testing is required of any female participant regardless of reported reproductive/menopausal status at screening.

#### **8.4.4 Appropriateness of safety measurements**

The porcine model has been extensively used as a model for studying human skin responses to medical devices. Compared to other common animal models, the epidermis and dermis of the pig has a thickness that is most similar to humans. The pig epidermis ranges from 30 to 140  $\mu\text{m}$ ; human skin ranges from 50 to 120  $\mu\text{m}$ . In addition, the skin of the pig is more firmly attached to the underlying structures as seen in humans ([Abdullahi et al., 2014](#)). Further, pig skin heals through re-epithelialization, unlike mice, rats, and other rodents whose skin heals through contraction. These features make the minipig a particularly useful model for evaluating the local and systemic effects of MIMIX MAPs as well as a useful model for determining if the MIMIX tip material will ultimately be absorbed or ejected and the likely timeline for this event in humans. Vaxess has carried out a pilot evaluation of MAP tolerability and tip persistence and a pilot repeat-dose systemic toxicology study in the Göttingen minipig model. We find that the minipig develops robust immune responses to the VX-103 vaccine antigen. In both pilot studies the results showed transient erythema and edema at the MAP application site that resolved by 28 days post MAP application. The erythema and edema reported, characteristically resolves in the first several days, then reappears and resolves by 28 days. No detectable adverse safety findings were reported. The pilot implantation effects study provides evidence that, by day 90, tip material for MIMIX FLU test articles is absorbed or ejected, there is no longer inflammation, and tissue has been restored to normal structure.

In sum, no adverse systemic events have been reported to date in our preclinical safety studies and local reactogenicity has been limited to transient erythema and edema. These data have been used to inform the design of the Phase 1 clinical trial.

#### **8.5 Additional assessments**

##### **8.5.1 Immunogenicity**

To describe the immunogenicity of VX-103, serum samples for determination of HAI antibodies will be collected at the time points defined in the Assessment Schedule ([Table 5](#)).

HAI titers, virus microneutralization titers, anti-HA, anti-fibroin IgG and total IgE will be assessed in serum of all participants, including the placebo group.

Instructions are outlined in the lab manual regarding tube handling, sample collection, numbering, processing, and shipment. In order to better define immunogenicity, the timing of the serum sample collection may be altered based on emergent data.

Serum samples remaining after completion of analysis may be used for exploratory assessment or other bioanalytical purpose (e.g., other bioanalytical exploratory assessments).

##### **Immunogenicity parameters**

The immunogenicity of the study vaccine will be evaluated primarily by measuring the number of participants who demonstrate seroconversion by developing a four-fold rise in the HAI titer following vaccination HAI titers. Mean fold rises in geometric mean HAI titers will be compared

across treatment groups at each timepoint. Immunogenicity of the vaccine will also be evaluated by measuring an increase in serum microneutralization titers and anti-HA IgG titers postvaccination. Standard statistical tests will be used to define a significant rise in antibody titers.

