| 
 
To assess the immunogenicity of VX-103 delivered in a single MIMIX MAP dose regimen in healthy adults in <math>\geq 18</math>-39 years of age.
 
To assess VX-103 MIMIX MAP delivery as a dose sparing skin immunization strategy by comparing the safety, reactogenicity, tolerability and immunogenicity of a fractional H1 vaccine dose level (7.5 <math>\mu\text{g}</math>) delivered by MIMIX MAP to a standard H1 vaccine dose level (15 <math>\mu\text{g}</math>) delivered by MIMIX MAP.
 
 |  | 
 
Influenza A H1 geometric mean HAI titer; mean fold rise and seroconversion rates for each treatment group and timepoint on Days 1, 29, 57, 85, 119, 180.
 
MIMIX MAP dose level comparisons in vital signs, laboratory parameters of hematology, clinical chemistry, urinalysis, adverse events, and local and systemic solicited and unsolicited reactogenicity event(s)
 
Influenza A H1 geometric mean HAI titer; mean fold rise and seroconversion rates for each route and timepoint for the fractional dose versus full dose delivered by MIMIX
 
 |  |
| Exploratory objective(s)                                                                                                                                                                                                                                                                                                                                                                                                                                                                                                                                  |  | Endpoint(s) for exploratory objective(s)                                                                                                                                                                                                                                                                                                                                                                                                                                                                                                                                                                              |  |

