| 
 
To assess seroprotection rates, anti-H1 HA IgG, virus microneutralizing (MN) titers, anti-fibroin IgG and total IgE titers to the influenza vaccine
 
                                                                                                                                                                                                                                                                                                                                                     |  | 
 
Influenza A H1 seroprotection rate for each treatment group on Days 1, 29, 180 by HAI and anti-influenza A H1 HA GMT, virus MN titers, anti-fibroin IgG, and total IgE for each treatment group on Days 1, 29, 180
 
                                                                                                                                                                                                                                                                                                                                                  |  |
| 
 
To evaluate the durability of the immune response for each vaccine dose level
 
                                                                                                                                                                                                                                                                                                                                                                                                                           |  | 
 
Influenza A H1 seroconversion rate, GMT, fold increase in GMT and SPR by HAI on Days 29 and 180 for treatment group
 
                                                                                                                                                                                                                                                                                                                                                                                                                                                 |  |

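### Arms are compared on HAI fold rise with no baseline adjustment stated, and the exploratory durability endpoint omits Days 57, 85 and 119, which are already collected

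*Protocol*

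**What the plan says.** Section 8.5.1 (Immunogenicity parameters) evaluates immunogenicity mainly by seroconversion. For magnitude it then says "Mean fold rises in geometric mean HAI titers will be compared" "across treatment groups at each timepoint". No model or covariate is named. The last sentence of that paragraph adds "Standard statistical tests will be used to define a significant rise in antibody titers". Section 12.5.3 lists GMTs, pre-to-post change in GMT by arm, seroconversion and seroprotection, again without adjustment.

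In Table 1 the secondary HAI endpoints are given "for each treatment group and timepoint on Days 1, 29, 57, 85, 119, 180". The dose comparison is given "for each route and timepoint for the fractional dose versus full dose delivered by MIMIX". The exploratory aim "To evaluate the durability of the immune response for each vaccine dose level" has the endpoint "Influenza A H1 seroconversion rate, GMT, fold increase in GMT and SPR by HAI on Days 29 and 180 for treatment group".

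Section 3 and Table 2 give 1:1:1 allocation with 15 per arm. Section 12.8 bases the 45 participants on historical practice and gives no SD, effect size, alpha or power.

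**The concern.** On the log scale a fold rise is a change score: post-dose minus baseline, with the baseline coefficient fixed at 1. When the true regression of post-dose on baseline titre has a slope below 1, this over-corrects. An arm that happens to start higher then shows a smaller rise for that reason alone.

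Such imbalance is plausible here. The arms are small, section 6.3.2 names no stratification by pre-titre, and the seroconversion definition provides for pre-titres both below and at or above 1:10. The contrast affected is 7.5 versus 15 µg, a secondary objective. The Day 1 titre needed to remove the imbalance is already drawn.

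On durability, sections 1.1 and 1.2 motivate the platform by waning immunity and by responses more than a month after dosing. The row of Table 1 meant to address durability nevertheless uses only the first and last post-dose HAI days.

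**Working it through.** The protocol has no precision figure to reproduce. The only arithmetic in section 12.8 is 30 + 15 = 45, or 15 per arm, which is consistent.

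**Inputs.** n = 15 per arm (Table 2). Post-dose days are 29, 57, 85, 119 and 180 (Table 1). The SD of log10 titre (s) and the pre/post correlation (ρ) are assumptions; s = 0.5 and ρ = 0.3, 0.5, 0.7 are used, with other SDs below.

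**Variance per participant, general form**
- Change score: s_pre² + s_post² − 2ρ·s_pre·s_post
- Analysis of covariance (ANCOVA): s_post²(1 − ρ²)
- Difference: (s_pre − ρ·s_post)², which is never negative

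Fold rise is therefore never asymptotically more precise than adjustment. The two are equal when s_pre = ρ·s_post.

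**Equal SDs.** The formulas become 2s²(1 − ρ) and s²(1 − ρ²), so the ratio ANCOVA/change is (1 + ρ)/2. Estimating the slope costs a factor of about 1 + 1/(2n − 5) = 1.04 at n = 15. The simulated ratios come from 20,000 trials per ρ.

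| ρ | (1+ρ)/2 | Simulated at n = 15 | 95% CI factor, fold rise | 95% CI factor, ANCOVA |
|---|---|---|---|---|
| 0.3 | 0.65 | 0.68 | 2.77 | 2.31 |
| 0.5 | 0.75 | 0.79 | 2.37 | 2.14 |
| 0.7 | 0.85 | 0.89 | 1.95 | 1.87 |

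The CI factor multiplies or divides the GMT ratio. It is 10^(t·SD·√(2/15)), with t on 28 df (fold rise) or 27 df (ANCOVA, including the 1.04). At ρ = 0.5 the fold-rise SD is 0.5, so 10^(2.048 × 0.5 × 0.365) = 2.37.

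**Other SDs at ρ = 0.5**, fold rise to ANCOVA: s = 0.4, 1.99 to 1.84; s = 0.6, 2.81 to 2.49; s = 0.7, 3.34 to 2.91.

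**Chance imbalance (equal SDs).** The standard error of the baseline difference is 0.5 × √(2/15) = 0.183 log10, or 1.52-fold. The fold-rise ratio shifts by 10^((1 − ρ) × 0.183), which is 1.34, 1.23 and 1.13 at ρ = 0.3, 0.5 and 0.7. At ρ = 0.5 the shift is 1.18, 1.29 and 1.34 for s = 0.4, 0.6 and 0.7. In simulation the fold-rise contrast correlates with baseline imbalance at −0.59, −0.50 and −0.38; the ANCOVA contrast correlates at about 0.

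**Unequal SDs.** With s_post = 0.5, s_pre = 0.25 and ρ = 0.5, the change-score variance is 0.0625 + 0.25 − 0.125 = 0.1875 and the ANCOVA variance is 0.25 × 0.75 = 0.1875. There is no gain, and ANCOVA bears the small-sample cost.

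**Durability.** For a linear slope on day, the sum of squares about the mean is 13,696 with five visits and 11,400.5 with Days 29 and 180. The five-visit variance is 11,400.5/13,696 = 0.83 of the two-visit variance if residuals are independent. It is 0.93 to 0.999 with residual autocorrelation of 0.3 to 0.8 per 28 days.

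**The case against.** The strongest reply is that the protocol names no model, so the lack of adjustment is read from silence. Covariates are commonly settled in the SAP, which is not at hand. An ANCOVA of log fold rise on log baseline would also give the same arm contrast as an ANCOVA of log titre. This stands in part: adjustment is not excluded. But section 8.5.1 does choose the statistic to be compared, and Table 1 does fix the durability days, so both can be improved as written.

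The equal-SD assumption is also open to challenge. Section 5.2 excludes people with influenza vaccination or diagnosed influenza in the previous 24 months, which could narrow baseline titres and shrink the gain. That stands as a limit on its size.

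A reader might infer more than the text supports:

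- **That fold rise ignores baseline or is biased.** It uses baseline with slope 1, and randomisation keeps it unbiased on average. The shift arises only given an imbalance.
- **That Days 57, 85 and 119 are discarded.** They are in the secondary HAI endpoints, and the dose comparison is also made per timepoint. They are missing only from one exploratory row.
- **That the sentence on a significant rise is the dose test.** It concerns a rise in titres, not the contrast between doses.
- **That a non-significant difference will be taken as dose sparing.** The protocol states no such rule, makes no power claim and calls the study exploratory.

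**Conclusion.** The point holds as a modest, inexpensive improvement to stated text. Fold rise is a valid comparison, but asymptotically it is at best as precise as adjustment for log baseline. Under equal SDs and ρ of 0.3 to 0.7, adjustment removes about 11% to 32% of the variance at 15 per arm, together with the dependence on chance imbalance. The gain falls to nil as the baseline SD approaches ρ times the post-dose SD.

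Adjustment does not cure the small sample. With s = 0.5 the interval still spans a factor of about 1.9 to 2.3 each way, against 1.9 to 2.8 with fold rise.

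The durability restriction costs at most about 17% of slope variance, and almost nothing under strong autocorrelation. The greater losses within that endpoint are the shape of waning and the intermediate titres of anyone who misses Day 180.

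The reference to route in the dose-comparison row is a clerical slip, since only MAP delivery is studied.

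**What to change.** - **Sections 8.5.1 and 12.5.3:** state that arms are compared by baseline-adjusted GMT ratios, from log post-dose HAI titre with log Day 1 titre as covariate. Give 95% CIs at each post-dose visit for 7.5/15 µg and for each dose versus placebo. Keep the geometric mean fold rise and seroconversion as planned summaries. A repeated-measures version over the five visits is optional.
- **Table 1, durability row:** add Days 57, 85 and 119.
- **Table 1, dose-comparison row:** replace the reference to route with dose level, as a wording correction only.
- **Reporting:** present 7.5 versus 15 µg as an estimated ratio with its interval.

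The cost is wording in two sections and one table. No samples, visits or participants are added.

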|  | 
 
○ Standard descriptive demography. All participants who receive any investigational product will be included in the safety analyses.
 
○ Proportion of participants in each treatment group with any non-zero report will be tabulated for each local and systemic solicited and unsolicited reactogenicity event; groups will be compared by Fisher's exact test (alternatively, a Cochran-Mantel-Haenszel [CMH] test will be used to analyze events by ordinal severity category).
 
○ Participants with adverse events (including clinical laboratory abnormalities) will be summarized by Medical Dictionary for Regulatory Activities (MedDRA) body organ system and preferred term, severity, relatedness and, separately, by seriousness.
 
○ Proportion of participants in each treatment group with AE reports within each body organ system will be compared in the same manner. Significant heterogeneity will be probed at the preferred term level.
 
 
b) Immunogenicity Parameters
 
 
○ Sera collected will be analyzed for determination of HAI titers. Serum IgG anti-H1 HA, virus microneutralization titers, serum IgE and anti-silk fibroin by Enzyme-linked immunosorbent assay (ELISA) will be assessed on (vaccination day), and on Days 29 (<math>\pm 1</math>), and 180 (<math>\pm 5</math>).
 
 
The results of these determinations will be evaluated as follows:
 
 
● Calculation of the geometric mean of pre- and post-vaccination HAI and anti-H1 HAI IgG serum antibody titers for each treatment group.
 
● Change from pre- to post-vaccination in geometric mean HAI and anti-H1 HAI IgG titers for each treatment group.
 
● Seroconversion rate defined as percentage of participants with either a pre-vaccination HAI titer <math>< 1:10</math> and post vaccination HAI titer of <math>\geq 1:40</math> or a pre-vaccination HAI titer of <math>\geq 1:10</math> and a minimum four-fold rise in post vaccination HAI antibody titer at each timepoint.
 
● Seroprotection rate defined as the percentage of participants with a HAI titer <math>\geq 1:40</math> at each timepoint
 
● Calculation of the geometric mean of pre- and post-vaccination influenza virus microneutralization titers
 
● Change from pre- to post-vaccination in geometric mean microneutralization titers
 
● Calculation of the geometric mean of pre- and post-vaccination anti-silk fibroin serum IgG antibody titers for each treatment group.
 
● Change from pre- to post-vaccination in geometric mean anti-silk fibroin IgG titers
 
● Calculation of the geometric mean of pre- and post-vaccination total serum IgE titers
 
● Change from pre-to post-vaccination in geometric mean total IgE titers
 
 |

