## 12.6 Analysis of exploratory endpoints

Exploratory analyses will include evaluations of seroprotection status (defined as an HAI titer of  $\geq 1:40$ ), H1 virus microneutralization titers, GMT of H1 HA specific IgG, total IgE titers, GMT of silk fibroin specific IgG and HAI titer against against a drifted H1 strain. These endpoints will be assessed on (vaccination day), and on Days 29 ( $\pm 1$ ), and 180 ( $\pm 5$ ).

Sera analyzed for determination of HAI, serum anti-H1 HA IgG, virus microneutralization titers, total serum IgE and anti-silk fibroin by ELISA results will be evaluated as follows:

- Calculation of the geometric mean of pre- and post-vaccination HAI titers for each treatment group for a drifted H1 strain.
- Calculation of the geometric mean of pre- and post-vaccination anti-H1 IgG serum antibody titers for each treatment group for the vaccine H1 strain.

- Change from pre- to post-vaccination in geometric mean anti-H1 IgG for each treatment group for the vaccine H1 strain.
- Calculation of the geometric mean of pre- and post-vaccination anti-silk fibroin IgG serum antibody titers for each treatment group.
- Change from pre- to post-vaccination in geometric mean anti-silk fibroin IgG titers.
- Calculation of the geometric mean of pre- and post-vaccination total serum IgE titers
- Change from pre-to post-vaccination in geometric mean total IgE titers

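### The exploratory microneutralization and anti-HA IgG responses are judged by a significant post-vaccination rise with no comparator named, although placebo sera are assayed and HAI is compared across arms

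*Protocol*

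**What the plan says.** The subsection on immunogenicity parameters in Protocol section 8.5.1 applies two standards in one paragraph. For HAI, "Mean fold rises in geometric mean HAI titers will be compared" across treatment groups at each timepoint. For the other two assays the text reads: "Immunogenicity of the vaccine will also be evaluated by measuring an increase in serum microneutralization titers and anti-HA IgG titers postvaccination". The paragraph then ends: "Standard statistical tests will be used to define a significant rise in antibody titers". No test, significance level, sidedness or comparator is given.

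The analysis sections do not fill the gap:

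- Section 12.6 lists, for anti-HA IgG, geometric means before and after vaccination and "Change from pre- to post-vaccination in geometric mean anti-H1 IgG for each treatment group for the vaccine H1 strain". It names microneutralization in its introduction but has no calculation bullet for it.
- The endpoint parameters in the synopsis list geometric means and "Change from pre- to post-vaccination in geometric mean microneutralization titers", with no contrast between arms.
- Table 1 ranks both assays as exploratory and lists them for each treatment group on Days 1, 29 and 180.

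Two other statements bear on the point. Earlier in section 8.5.1 the protocol says: "HAI titers, virus microneutralization titers, anti-HA, anti-fibroin IgG and total IgE will be assessed in serum of all participants, including the placebo group". The study design entry of the synopsis says that immunogenicity, with safety and tolerability, is described in comparison with placebo.

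**The concern.** A rise is most naturally read as a change from baseline. If its significance is tested in one arm alone, the null hypothesis is that the mean log titer change in that arm is zero. That hypothesis is false whenever something other than the vaccine moves titers in every arm. Exposure to circulating H1 virus during the 180 days of follow-up is one possibility; a shift in the assay between baseline and post-dose runs is another. The test cannot separate either from a vaccine effect.

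The randomised placebo arm is there to make that separation, and its sera are assayed for both endpoints. As section 8.5.1 is written, nothing ties that arm to the test. At stake is whether a reported significant microneutralization or IgG response to 7.5 µg or 15 µg can be attributed to the vaccine.

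**Working it through.** **1. The plan's own figures.** Section 12.8 gives 30 participants on active treatment and 15 on placebo, and section 6.1.3 gives 1:1:1 allocation. 3 × 15 = 45 and 2 × 15 = 30, so these agree. The protocol states no power, effect size, SD or significance level for these assays, so there is no further figure to reproduce.

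**2. What each place specifies.**

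| Place | HAI | Microneutralization | Anti-HA IgG |
|---|---|---|---|
| 8.5.1 | fold rise compared across groups | increase after vaccination, then a test of rise | increase after vaccination, then a test of rise |
| 12.6 | drifted strain: geometric means per group | introduction only | geometric means and change per group |
| Synopsis, endpoint parameters | geometric means, change, seroconversion, seroprotection | geometric means, change | geometric means, change |

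No row gives a contrast with placebo for microneutralization or anti-HA IgG.

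**3. Illustration: inputs.** n = 15 per arm is from the protocol. The rest is assumed, because the protocol is silent: two-sided 5%; t-tests on the log2 change from baseline; SD of that change 1, 1.5 or 2 log2; no vaccine effect; and a mean rise d that is the same in every arm.

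**4. Within-arm test.** The statistic has 14 degrees of freedom, critical value 2.145 and noncentrality d√15/SD. The probability of a significant rise is the upper-tail probability of the noncentral t beyond 2.145.

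For d = 0.5 log2 (2^0.5 = 1.41-fold):

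- SD 1: noncentrality 0.5 × 3.873 / 1 = 1.936, probability 0.438
- SD 1.5: 0.5 × 3.873 / 1.5 = 1.291, probability 0.225
- SD 2: 0.5 × 3.873 / 2 = 0.968, probability 0.145

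Simulation with 40,000 trials per setting gives 0.439, 0.224 and 0.144. The wider range is:

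| Shared rise | SD 1 | SD 1.5 | SD 2 |
|---|---|---|---|
| none | 0.025 | 0.025 | 0.025 |
| 0.25 log2 (1.19-fold) | 0.145 | 0.087 | 0.066 |
| 0.5 log2 (1.41-fold) | 0.438 | 0.225 | 0.145 |
| 1 log2 (2-fold) | 0.949 | 0.671 | 0.438 |

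These count significant rises only. With no shared change, 2.5% is the favourable half of the nominal 5%.

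**5. Contrast with placebo.** The shared rise d cancels in the difference between arms, so the noncentrality is 0 and the favourable-tail rate is 0.025 in every cell. Simulation at d = 0.5 and d = 1 gives 0.024 to 0.025.

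**6. Power given up.** The two-sample test has 28 degrees of freedom, critical value 2.048 and noncentrality δ/(SD√(2/15)), where δ is the true vaccine effect. For a 4-fold effect (δ = 2 log2) at SD 1.5 this is 2/(1.5 × 0.365) = 3.651, and power is 94%. The one-sample test has noncentrality 2 × 3.873 / 1.5 = 5.164 and power above 99%. At SD 1 and SD 2 the two-sample power is above 99% and 75%. For a 2-fold effect it is 75%, 42% and 26% at SD 1, 1.5 and 2.

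**The case against.** The strongest reply is that an unspecified test is not a wrong one. The closing sentence of section 8.5.1 speaks of antibody titers generally, does not say that the test is within an arm, and follows a sentence that compares HAI across groups. The exact test for an exploratory assay is commonly left to the SAP, which is not shown. The synopsis also states a comparison with placebo. All of this is true, and it rules out saying that the protocol prescribes a one-sample test. It does not remove the problem. The protocol names a criterion, a significant rise, and uses it to evaluate the vaccine. The comparison intended in the synopsis is not carried into the sections that say how these two assays are judged.

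Two stronger readings are tempting and are not supported:

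- A reader might infer that any shared change would be credited to the vaccine. Placebo is one of the treatment groups for which results are tabulated, so a shared rise would be visible beside the active arms. The supported statement is that a significance claim made arm by arm could mislead.
- A reader might infer that the Day 180 durability conclusion is exposed. The durability endpoint in Table 1 rests on HAI, whose fold rises section 8.5.1 does compare across groups.

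It is also fair that the error rates depend on an assumed drift and SD, and that nothing in the protocol says baseline and later sera are assayed in separate runs.

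**Conclusion.** The point holds as a cheap improvement to exploratory analyses. It does not touch the primary safety objective or the HAI analyses. For microneutralization and anti-HA IgG, section 8.5.1 fixes a criterion without a control, and no analysis section adds one, although the control data will exist.

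The size is conditional. If all arms rise by 0.5 log2 and the vaccine does nothing, a within-arm test at n = 15 flags a response in about 44%, 22% or 14% of trials at SD 1, 1.5 or 2 log2. If nothing shared occurs, the test holds its nominal 5%. The placebo contrast holds its level either way. These figures assume roughly normal log2 changes and a shift that is equal across arms; they do not estimate what will happen in this trial.

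**What to change.** Amend sections 8.5.1 and 12.6 along these lines: for microneutralization and anti-HA IgG, the response at Days 29 and 180 is judged by the ratio of geometric mean titers of each dose to placebo, with a 95% confidence interval, from a model of log titer on treatment and log baseline titer; fold rises within an arm are descriptive only. Add the missing microneutralization entry to section 12.6 at the same time, so that both sections and the synopsis agree.

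The cost is wording and one model per assay. No new samples or assays are needed. The downside is some nominal power relative to a one-sample test: about 94% instead of above 99% for a 4-fold effect at SD 1.5 log2, before any gain from baseline adjustment. A 2-fold effect would often be missed at 15 per arm, so the interval should carry the interpretation.
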